*i.e.* production of hormones such as insulin) and exocrine (
*i.e.* production of enzymes to aid digestion) functions are critical for nutritional metabolism and in chronic diseases including diabetes. Furthermore, deficits in exocrine and endocrine functions may interact such that diabetes is common among people with exocrine pancreas insufficiency
^
12
^ and low faecal elastase is common in patients with type 2 diabetes, especially those with poor glycaemic control.
^
13
^ There is a dearth of studies explaining the mechanisms of the exocrine-endocrine interactions leading to abnormalities in both functions.

In spite of its central importance, there has been surprisingly little research on pancreatic function following recovery from wasting malnutrition. This is likely due, in part, to there being no validated, easily measurable indicator of prior wasting malnutrition, in contrast to studies of poor early linear growth, resulting in largely irreversible stunting, short legs, and increased sitting/standing height ratio in adulthood. There is thus an urgent need for prospective cohort studies to investigate long-term effects of wasting malnutrition.

The central hypothesis of the severe acute malnutrition in children and adults - the role of the pancreas (SAMPA) study is that an episode of wasting malnutrition, irrespective of age of occurrence, affects endocrine and exocrine pancreatic size, structure and function. The study will recall for cross-sectional investigations participants from established cohorts recruited for the research team’s previous studies in Tanzania, Zambia, India and the Philippines. Many cohort members were originally recruited because of an episode of severe malnutrition or their infection with HIV or tuberculosis; their prior nutritional status, plus those of well-nourished controls, is documented. The cohorts now range in age from adolescence to late middle age and live in places with a wide range of access to foods high in fat and sugar which, combined with a more sedentary lifestyle, could affect their risk of diabetes. We will assess the association of prior wasting malnutrition with current pancreas structure and function, taking into account factors such as sex, current age, time since malnutrition, current BMI and body composition, and infections which could affect pancreas functions.
Figure 1 shows the conceptual framework guiding the programme of research.

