### Study cohorts

This study brings together diverse cohorts (
Table 1) under a common theme providing participants with prospectively assessed and clearly defined malnutrition exposure across populations and life-course and not previously malnourished controls, all from LMICs at various stages of the nutrition transition but with ongoing burden of infectious disease. Flow charts for each cohort are given in
Figures 2–
7.

**Table 1. T1:** Study cohorts for Severe Acute Malnutrition in children and adults - the role of the Pancreas (SAMPA).

	Cohort	Sample size-previous and expected
**1.**	** *DIVIDS (Delhi Infant Vitamin D Supplementation) study, India* ** The DIVIDS cohort comprises infants born low birth weight (LBW, <2.5 kg) at term in 2007-2010. They had monthly follow-up until 6 months ^ 14 ^ then at 5 years ^ 15 ^ and are currently, aged ~13 years. *For SAMPA, the DIVIDS cohort acts as a positive control since we expect adverse long-term non-communicable disease consequences of being born LBW.*	• Birth: 2079 total, all LBW • Age 5 y: 912 total, 764 (84%) BMIZ>-2, 138 (15%) BMIZ -2 to -3, 9 (1%) BMIZ<-3; 1 no anthropometry • Age ~13 y (ongoing): 647 total, 482 (75%) BMIZ>-2, 117 (18%) BMIZ -2 to -3, 48 (7%) BMIZ<-3 • Expected for SAMPA: 750 total
**2.**	** *SAM (Severe Acute Malnutrition), Lusaka, Zambia* ** This group comprises: a) 100 children who were hospitalised with malnutrition at University Teaching Hospital (UTH) between 2010 and 2014 when they were < 2 years b) 85 never-malnourished neighbourhood controls. Children were aged ~9 years at previous follow-up ^ 16 ^ and will be ~12 years for SAMPA.	• Age < 2 y: 100 malnutrition • Age 9 y: 185 total, 100 previous malnutrition, 85 no malnutrition; currently 17 (9%) BMIZ <-2 • Expected for SAMPA: 180 total

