**5.**	** *St-ATT (Starting Anti-TB Treatment) Cohort, Philippines* ** Between Aug 2018 and Feb 2020, the St-ATT cohort recruited 900 adults undergoing tuberculosis treatment in three provinces: Cebu, Negros Occidental and Metro Manila, encompassing urban, peri-urban and rural populations. 17% had HbA1c >=7.0% (probable diabetes in TB) with an additional 30% with HbA1c 5.8%-7.0% (‘prediabetes’/mild TB-induced hyperglycaemia). ^ 21 ^ https://www.isrctn.com/ISRCTN16347615 *This cohort will be involved in the in-depth analyses.*	• 1-2 y prior: 900 total, 495 BMI >18.5 kg/m ^2^, 189 (21%) BMI 17.0-18.5 kg/m ^2^, 216 (24%) BMI <17 kg/m ^2^ • Expected for SAMPA: 600 total
**6.**	** *CLHNS (Cebu Longitudinal Health and Nutrition Survey), Philippines* ** The mothers of the cohort were randomly selected in 1983-84 when they were pregnant. ^ 22 ^ All singleton births were included regardless of nutrition status. Since the original bimonthly follow-up surveys up to age two years, there have been 8 follow-up surveys including in 2018-2019 when 1326, ~43% of the initial birth cohort (3,080), were available. *This cohort represents our longest follow-up of malnutrition diagnosed by anthropometry.* (Earlier cohort data are available open access: https://www.cpc.unc.edu/projects/cebu).	• Birth: 28 LBW of the 143 with childhood malnutrition • Age ≤ 2 y: of 420 total to be included, 143 (34%) WHZ<-3 • Expected for SAMPA: 420 total

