*Anthropometry*:** Anthropometry will use standard methods
^
27
^ conducted by trained staff. At each site technical error of measurement will be assessed and further training provided so that all staff reach acceptable levels of agreement with the local criterion anthropometrist.
^
28
^ Anthropometric measurements will be weight, height, sitting height, tibia length, circumferences of waist, hip and mid-upper arm, and triceps and subscapular skinfold thicknesses.7.
**
*Body composition:*
** All sites will use bioelectrical impedance (BIA) for body composition assessment. Lusaka will additionally use air displacement plethysmography (BodPod) and can assess its agreement with BIA.

The following assessments will be conducted in only subsets of consenting participants.
8.
**
*Detailed OGTT*
**: The same OGTT protocol will be used as above but, for 80 participants in each of the CICADA and St-ATT cohorts, referred to as the in-depth subset, we will measure additional hormones: glucagon, gastric inhibitory peptide (GIP), glucagon-like peptide-1 (GLP-1) at multiple time points and trypsinogen in baseline samples. The in-depth subsets will be randomly selected from the cohort participants, stratified by whether or not they were recorded as previously malnourished in our databases from earlier follow-ups. In event of refusals, replacements will be from the next in the randomised lists.9.
**
*IVGTT:*
** This test is the gold standard for estimating the early insulin response. It will be done only in the in-depth subset from CICADA. Results will be compared with OGTT in the same participants in order to better understand the OGTT results. For this test a solution of sterile 50% dextrose, in amounts 0.3 g/kg body weight, will be injected into the antecubital vein over 60 seconds starting at time 0 minutes. Blood samples will be taken at -10, -1, 2, 4, 6, 8, 10 minutes for measurement of glucose, insulin, C-peptide and glucagon.10.
**
*CT scans*
**: The CT studies will be performed in 100 participants from each of the adult cohorts by qualified and experienced radiologists in identified health facilities. Participants will be randomly selected, similarly to the in-depth subsets. Scans will be taken without use of contrast agents. The protocol will assess the following:•Pancreatic volume (in cm

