### Statistical analyses and sample size calculations

Analyses related to individual hypotheses are described below. Primary analyses will be conducted for each cohort separately. Pooled analyses using all or some cohorts combined will be conducted based on the individual cohort results, and in order to investigate how age at malnutrition and length of time between malnutrition and outcome assessment influence the associations between malnutrition and pancreas structure and function. Analyses will be guided by the conceptual framework in
Figure 1. Sample sizes for the specific hypotheses indicate that, with the available number of participants in the cohorts, we have sufficient power for the main analyses with all participants. For some expensive or labour- and participant-intensive outcomes, we had to consider cost and feasibility and have calculated power for analyses in subsets.

*Hypothesis 1:*
Prior malnutrition is associated with later abnormal pancreatic structure and endocrine and exocrine function.

Participants with and without prior wasting malnutrition, the SAMPA study primary exposure, will be compared within each cohort for all pancreas structure and function outcomes: diabetes by OGTT or HbA1c, exocrine function as indicated by faecal elastase and serum lipase, and pancreas size and presence of abnormalities detected by ultrasound or CT scan. We will initially fit regression models for each outcome with prior malnutrition as the main exposure, controlling for sex and for age as a continuous variable. We will investigate whether there are interactions between prior malnutrition and sex, which is known to be associated with both prior malnutrition and diabetes. We will then investigate whether the associations between malnutrition and the outcomes differ by the following variables:
•Time since malnutrition•Sitting/standing height ratio as an indicator of early life stunting•HIV status for African cohorts only (SAM Lusaka, NUSTART Lusaka, CICADA)

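### Early-life stunting is indexed only by the current sitting/standing height ratio, although CLHNS and DIVIDS must already hold childhood length or height

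*Protocol article*

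**What the plan says.** Under Hypothesis 1, the section on statistical analyses and sample size first compares outcomes by prior malnutrition with control for sex and age, then examines the interaction with sex. It then lists three further possible modifiers. The stunting item reads "Sitting/standing height ratio as an indicator of early life stunting". The item after it is restricted by cohort: "HIV status for African cohorts only (SAM Lusaka, NUSTART Lusaka, CICADA". The stunting item has no such restriction.

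The ratio comes from measurements at the SAMPA visit (Assessments, anthropometry): "Anthropometric measurements will be weight, height, sitting height, tibia length" are the first items on the list. The Introduction gives the rationale, describing poor early linear growth as "resulting in largely irreversible stunting, short legs, and increased sitting/standing height ratio in adulthood".

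Table 1 describes earlier data in two cohorts. For CLHNS, at ages up to 2 years, it gives "of 420 total to be included, 143 (34%) WHZ<-3". It describes the survey schedule as "Since the original bimonthly follow-up surveys up to age two years, there have been 8 follow-up surveys" and says that earlier data are openly available. For DIVIDS, on the infancy phase, it says "They had monthly follow-up until 6 months". It then reports BMI Z categories at 5 years for 912 children, only one of whom lacked anthropometry.

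**The concern.** The stunting modifier is meant to show whether the association of wasting with later pancreatic outcomes depends on early linear growth failure. As written, the plan infers early growth from body proportions many years later in all six cohorts. In at least two of them, early or mid-childhood linear growth was measured at the time.

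Two things are at stake. First, an indirect marker of the modifier dilutes the interaction, so a null result would be hard to interpret: it could mean that stunting plays no part, or that the ratio does not capture it well in that cohort. Second, the protocol's own reason for the ratio concerns adults, and the article offers no support for it at 12 or 13 years, the ages of the adolescent cohorts. The programme's stated strength is prospectively recorded nutritional history, and here that strength is not used.

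**Working it through.** The article states no sample size, power or correlation for this analysis, so there is no figure to reproduce. The check is mainly a comparison of sections.

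**1. Scope of the ratio.** It is the only stunting variable named. The neighbouring HIV item is limited to three cohorts and the ratio is not, so by implication it applies to all six. Anthropometry is listed among the assessments for all consenting participants.

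**2. Fit with its rationale.** The Introduction refers to adulthood. Table 1 puts DIVIDS at about 13 years and SAM Lusaka at about 12.

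**3. Whether direct data exist.**
- CLHNS: WHZ is weight for length or height. A count of children with WHZ below -3 by age 2 requires a measured length.
- DIVIDS: BMI is weight divided by height squared. BMI Z at 5 years for 911 of 912 children (912 - 1) requires a measured height. Length at the monthly infancy visits is not stated.
- SAM Lusaka: Table 1 reports BMI Z only at the follow-up at about 9 years, so no early-life length is shown.
- CICADA, NUSTART Lusaka and St-ATT: these enrolled adults, and no childhood length or height is described.

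**4. Number of participants concerned.** Expected totals are DIVIDS 750, SAM 180, CICADA 1412, NUSTART 300, St-ATT 600 and CLHNS 420.
- Sum: 750 + 180 + 1412 + 300 + 600 + 420 = 3662.
- CLHNS plus DIVIDS: 420 + 750 = 1170, or 1170 / 3662 = 32%.

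The 1170 is an upper limit. Table 1 does not say that all 750 DIVIDS participants were measured at 5 years, nor that all 420 CLHNS participants have a length at any given age.

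**5. Illustration of dilution (assumed correlations).** Let r be the correlation between the ratio and the childhood Z-score. Treat the Z-score as the true modifier and the ratio's error as unrelated to outcome. The noncentrality of the interaction z-test is then multiplied by r:

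power = Φ(r × (1.960 + z_power) - 1.960), and the required n is multiplied by 1/r².

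For 80% power with the direct measure, z_power = 0.842 and the bracket is 2.802. At r = 0.5, Φ(1.401 - 1.960) = Φ(-0.559) = 0.29.

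| Assumed r | Power if direct gives 80% | Power if direct gives 90% | Factor on n |
|---|---|---|---|
| 0.9 | 71% | 83% | 1.2 |
| 0.7 | 50% | 62% | 2.0 |
| 0.5 | 29% | 37% | 4.0 |
| 0.3 | 13% | 16% | 11.1 |

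The result depends wholly on r, which the article does not give. The starting powers of 80% and 90% are also assumptions, since the article claims adequate power only for its main analyses.

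**The case against.** The best defence is uniformity. The ratio can be measured in the same way in all six cohorts, three of which have no childhood data described, and pooled analyses are planned. A modifier defined differently by cohort is harder to compare. This is a good reason to keep the ratio, but not to use it alone, because the primary analyses are done cohort by cohort.

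The article calls the ratio an indicator, and a condensed article may leave cohort-level definitions to the analysis plan. That is fair as far as it goes. Even so, the article does fix a choice here, names no other stunting variable, and limits by cohort only the item beside it.

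The direct measures have their own limits. Height at 5 years is itself a later reading of early growth, so treating it as error-free in the illustration favours the alternative. Some participants may lack the record. Where the wasting index and the stunting Z-score come from the same visit, an error in length or height enters both. All of this stands.

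A reader might go further and infer that the ratio is a weak or noisy marker, or that pubertal timing distorts it in adolescents. The documents support neither. They give no validity figure, the Introduction presents the ratio as a lasting trace of poor early growth, and puberty is not mentioned. What they do show is that the marker is indirect and that its stated rationale is limited to adults.

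**Conclusion.** The point holds and is minor. The plan relies on one current, indirect marker of early stunting in every cohort, including two adolescent cohorts outside its stated rationale. CLHNS and DIVIDS must hold childhood length or height that the article does not plan to use for this purpose. That last step is an inference, though a firm one, because the reported Z-scores could not otherwise exist.

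The gain from using these records cannot be stated from the documents. The fall from 80% to between 71% and 13% is a range under assumed correlations, not an estimate. It would be tempting to say that 1170 participants are analysed with the wrong variable. The documents show only that up to 1170 belong to cohorts where a direct record exists for some or all members. No primary outcome, exposure definition or main comparison depends on this modifier.

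**What to change.** In the per-cohort analyses under Hypothesis 1, define the stunting modifier as length-for-age Z from the first two years in CLHNS and height-for-age Z at 5 years in DIVIDS, where recorded. Do not rely on infant length in DIVIDS unless the team confirms that it was measured. Keep the sitting/standing height ratio as the common measure in all six cohorts and for pooled analyses. Report its correlation with the childhood Z-score in CLHNS and DIVIDS: the CLHNS figure bears on its use in the adult cohorts, and the DIVIDS figure on its use in SAM Lusaka.

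The cost is linkage to records that the team already holds, plus a sentence or two of analysis text. There are three small downsides. The modifier differs between cohorts, which keeping the ratio alongside it addresses. Some participants may lack the childhood record, so the numbers available should be reported. Length or height can enter both the wasting index and the stunting Z-score. In CLHNS the two-monthly surveys may allow the Z-score to be taken from a different visit than the one that defines wasting. In DIVIDS the overlap should be acknowledged if both come from the 5-year visit.

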**3.**	** *CICADA (Chronic Infections, Co-morbidities and Diabetes in Africa), Mwanza, Tanzania* ** The CICADA cohort, ^ 17 ^ total n=1947, comprises three subgroups: a) Tuberculosis patients and controls from the TB-NUT study whose HIV and nutritional status ~16 years ago at recruitment are known (50% BMI<18.5 kg/m ^2^) as well as more recently recruited HIV-infected and uninfected people (controls) ^ 18 ^ ^,^ ^ 19 ^ b) NUSTART, conducted 2010-2014, was a two-site (Mwanza and Lusaka) trial of food supplements for malnourished (BMI<18.5 kg/m ^2^) HIV-infected adults, recruited when starting antiretroviral therapy. ^ 20 ^ In Mwanza, 704 participants were recruited, 409 were alive and followed at the 12-week NUSTART end-point; 273 were available at a follow-up two-three years after starting ART and 206 were recruited to the CICADA study. c) HIV-infected and uninfected people, both malnourished and well-nourished, recruited 3-four years ago for HIV, nutrition and diabetes assessments *CICADA has the most detailed longitudinal diabetes data of the project cohorts, archived fasting samples, and are the oldest so have had longer to develop diabetes; therefore, this cohort will be used for the in-depth and longitudinal components.*	CICADA (TB-NUT) 16 y prior: 450 total • 73 (16.2%) BMI <17 kg/m ^2^ • 74 (16.4%) BMI 17 to 18.5 kg/m ^2^ • 303 (67.4%) BMI > 18.5 kg/m ^2^ CICADA (NUSTART) 11 y prior: 208 total • 105 (50.5%) BMI <17 kg/m ^2^ • 103 (49.5 %) BMI 17 to 18.5 kg/m ^2^ CICADA (New HIV +/- cohort) 4 y prior: 1293 total • 109 (8.4%) BMI <17 kg/m ^2^ • 171 (13.3 %) BMI 17 to 18.5 kg/m ^2^ • 1009 (78.3%) BMI >18.5 kg/m ^2^ Expected for SAMPA: 1412 total
**4.**	** *NUSTART, Lusaka, Zambia* ** 200 previously malnourished HIV-infected adults will be traced and recruited from the NUSTART Lusaka participants. ^ 20 ^ We will also recruit 50 HIV-infected and 50 non-HIV-infected, not previously malnourished, neighbourhood controls.	• 10 y prior: 1111 total, 437 (39%) BMI 17 to 18.5 kg/m ^2^, 674 (61%) BMI<17 kg/m ^2^ • Expected for SAMPA: 300 total

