*i.e.* glucose, hormones, faecal elastase and serum lipase, the available sample size in the smallest cohort will be sufficient to determine differences of 0.4 times the standard deviation with 90% power. Expected differences in pancreas volume were calculated using volume normalised to kg body weight to account for the participant age and size range.
^
35
^ A total of n=100 per cohort (assuming a standard deviation of 0.3 mL/kg) will provide 90% power to detect differences of 0.2 mL/kg between those with/without prior malnutrition, which is a smaller difference than that expected between people with and without diabetes.
^
35
^
^,^
^
36
^

*Hypothesis 2:*
Prior malnutrition is associated with pancreatic calcification which in turn is associated with diabetes.

To investigate whether prior malnutrition is associated with pancreas calcification, from each adult cohort we will randomly select for CT scans 50 participants who were exposed to malnutrition and 50 controls who were not exposed. The presence of calcification or other pancreas abnormalities on CT will be compared between those with or without prior malnutrition.

In order to increase sample size for this and for the second part of the hypothesis comparing calcification with diabetes, results from CT scans in the subset of participants with these will be compared with the ultrasound results from the same participants to indicate whether abnormalities determined by ultrasound, e.g. pancreas body or duct shape, correspond to calcification by CT scan. We will then compare the proportion of abnormalities based on ultrasound or CT scan among those with and without diabetes.

**
*Sample size*
**: Population prevalence estimates for pancreatic calcification appear unavailable so we have not performed any sample size calculations. Pancreatic calcifications are seen in fibro-calculous pancreatic diabetes
^
7
^ but these studies have been conducted on participants selected for their clinical presentation.

*Hypothesis 3:*
The abnormal glucose regulation seen after malnutrition is associated with relative insulin deficiency with or without insulin resistance.

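### The 90% power claimed for a 0.4 SD difference in the smallest cohort does not hold for SAM Lusaka, where it is about 76% at a two-sided 5% level

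*Protocol article*

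**What the plan says.** Under Statistical analyses and sample size calculations, Hypothesis 1, Sample size, the protocol article gives one power statement for the continuous outcomes, which it lists as "glucose, hormones, faecal elastase and serum lipase". It says that "the available sample size in the smallest cohort will be sufficient to determine differences of 0.4 times the standard deviation with 90% power".

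The same section sets the unit of analysis: "Primary analyses will be conducted for each cohort separately". Participants with and without prior malnutrition "will be compared within each cohort for all pancreas structure and function outcomes". Pooled analyses come afterwards.

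Table 1 (Study cohorts) gives the cohort sizes. For SAM Lusaka it has "Expected for SAMPA: 180 total", and for the previous follow-up "Age 9 y: 185 total, 100 previous malnutrition, 85 no malnutrition". For NUSTART Lusaka it has "Expected for SAMPA: 300 total", made up of 200 previously malnourished adults and 100 controls (50 HIV-infected and 50 not). The other cohorts are expected to provide 420 (CLHNS), 600 (St-ATT), 750 (DIVIDS) and 1412 (CICADA).

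**The concern.** The sentence rests its assurance on the smallest cohort, so that a reader takes every larger cohort to be at least as well placed. By Table 1 that cohort is SAM Lusaka, and a total of 180 looks too small: 90% power at 0.4 SD usually needs more than 130 per group.

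Faecal elastase and serum lipase are listed as primary outcome measures for exocrine function, and this sentence is the only power statement that covers them. The section's general statement that power is sufficient for the main analyses with all participants depends in part on it. SAM Lusaka is also the only cohort in Table 1 defined by hospital admission for malnutrition in early childhood with never-malnourished controls. If its power is overstated, a reader who relies on the sentence could give a null result there more weight than it can bear.

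**Working it through.** **Inputs.** Difference d = 0.4 SD and target power 90% (Hypothesis 1, Sample size). SAM Lusaka: 180 expected and an earlier split of 100:85 (Table 1). Scaled to 180, this is 180 × 100/185 = 97.3 and 180 × 85/185 = 82.7, so about 97 v 83. NUSTART Lusaka: 200 v 100 (Table 1). Significance level and sidedness are not stated; two-sided 5% is assumed and one-sided 5% is also tried. No allowance for loss is made, since 180 is already the expected number.

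**Formula.** Comparison of two means, normal approximation: power = Φ(d / √(1/n₁ + 1/n₂) − z), with z = 1.960 (two-sided 5%) or 1.645 (one-sided 5%). Each result was checked with the noncentral t distribution.

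**Step 1: where the plan's figure can be reproduced.** NUSTART Lusaka, 200 v 100: √(1/200 + 1/100) = 0.1225; 0.4/0.1225 = 3.266; 3.266 − 1.960 = 1.306; Φ(1.306) = 90.4% (noncentral t 90.2%). The stated 90% fits this cohort.

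**Step 2: the smallest cohort.** SAM Lusaka, 97 v 83: √(1/97 + 1/83) = 0.1495; 0.4/0.1495 = 2.675; 2.675 − 1.960 = 0.715; Φ(0.715) = 76.3% (noncentral t 75.8%).

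**Step 3: sensitivity to the assumptions.**

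| SAM Lusaka split | Two-sided 5%, normal | Two-sided 5%, noncentral t | One-sided 5%, normal |
|---|---|---|---|
| 90 v 90 | 76.5% | 76.1% | 85.1% |
| 97 v 83 | 76.3% | 75.8% | 84.9% |
| 100 v 80 | 76.0% | 75.6% | 84.7% |
| 100 v 85 (all 185) | 77.4% | 77.0% | 85.7% |

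The split hardly matters. Of the levels tried, only a one-sided 10% level takes SAM Lusaka above 90% (about 92%).

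**Step 4: what SAM Lusaka can detect.** Detectable difference = (z + z_power) × √(1/n₁ + 1/n₂). At 90% power: (1.960 + 1.282) × 0.1495 = 0.485 SD (noncentral t 0.487). At 80% power: (1.960 + 0.842) × 0.1495 = 0.42 SD.

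**Step 5: size needed for the claim.** Per group, 2 × (1.960 + 1.282)² / 0.4² = 131.4, so 132 (133 by noncentral t), against about 97 and 83 available.

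**The case against.** The strongest defence is that the article fixes no significance level, so 76% is conditional. That is true and has to be declared, but one-sided 5% still gives only about 85%. The adjoining pancreas volume statement (50 v 50, difference 0.2, SD 0.3, 90% power) gives 91.0% at two-sided 5% and 95.2% at one-sided 5%, so two-sided 5% is the more natural reading of the section. It does not settle the matter.

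A second defence is adjustment for age and sex, which raises power somewhat. If the covariates explained 10% of the outcome variance, power would be about 80%; at 20%, about 85%. Reaching 90% would take nearly one third of the variance, and the article assumes nothing of the kind.

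A third is that only adult cohorts were meant. That may be how the figure arose, but it is an inference. The sentence has no such limit, and the Hypothesis 1 text names SAM Lusaka among the cohorts to be analysed. Later pooling does not help either, because the claim concerns a single cohort.

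It also stands that the cohort is of fixed size, that the design would not change, and that at 80% power the detectable difference of 0.42 SD is close to the stated 0.4.

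Three stronger readings are tempting and are not supported:

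- A reader might infer that NUSTART Lusaka falls short too, because only 50 of its controls are HIV-infected like the exposed group. The protocol compares those with and without prior malnutrition within the cohort and lists HIV status only as a variable by which associations may differ. It does not plan a main comparison limited to HIV-infected controls.
- A reader might infer that every hormone outcome is affected in SAM Lusaka. Incretins and glucagon during the OGTT are measured only in CICADA and St-ATT subsets, and for the modelled OGTT indices in children, data from groups of participants are to be combined.
- A reader might infer that the 2-hour glucose outcome is underpowered because of this error. That outcome is binary (7.8 mmol/L or above), and its power is stated separately for CICADA and St-ATT.

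**Conclusion.** Wrong as written. The article's own Table 1 contradicts the power claimed for the smallest cohort. Assuming a two-sided 5% level and about 97 v 83, SAM Lusaka has about 76% power for 0.4 SD, so the type II error is about 24% where 10% is stated. The range is 76% to 77% over plausible splits and the full 185, and about 85% if the test were one-sided at 5%. With 90% power the cohort can detect about 0.49 SD.

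The finding is limited to SAM Lusaka and to the continuous outcomes measured there: glucose, insulin, C-peptide, baseline proinsulin, faecal elastase and serum lipase. It does not show that the other cohorts are short of power, that the design is unsound, or that more participants must be found. That the figure was worked out for NUSTART Lusaka is a plausible explanation, not something the article says.

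**What to change.** Replace the sentence with wording to this effect:

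*Assuming a two-sided 5% level, in the smallest cohort (SAM Lusaka, about 97 v 83) there is 76% power for a difference of 0.4 SD and 90% power for 0.49 SD; NUSTART Lusaka (200 v 100) has 90% power for 0.4 SD.*

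If the investigators intended another level or a one-sided test, they should state it and give the matching figures. The cost is one sentence and a less favourable figure for SAM Lusaka. No change to recruitment, measurement or analysis is needed.
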